#### 2.7.2. Covariables

Anthropometric data such as age, gender, and body mass index, and clinical data such as weeks since infection, and comorbidities assessed with the Charlson comorbidities index [36,37] will be recorded.

### 2.8. Sample Size Calculation

An a priori sample size was based on the minimum clinically important difference (MCID) of the BPI interference estimated to be 1.00 [50]. Using G*Power 3.1.9.2, we obtained a sample size of 49 participants, equally distributed between the treatment and control groups, based on a confidence level of 95% (α = 0.05) and a power of 80% (β = 0.2). Anticipating a 20% dropout rate, the total sample size was increased to ensure adequate statistical power and the resulting sample size was 30 participants per group.

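### Section 2.8 does not add up: 49 cannot be split equally, 60 enrolled less 20% dropout leaves 48, and the SD behind 49 is not given

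*Protocol article*

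**What the plan says.** Section 2.8 of the protocol article is the only justification of the sample size. The calculation is "based on the minimum clinically important difference (MCID) of the BPI interference estimated to be 1.00", with α = 0.05 and 80% power. The result is given as follows: "Using G*Power 3.1.9.2, we obtained a sample size of 49 participants, equally distributed between the treatment and control groups". After a 20% dropout allowance, "the resulting sample size was 30 participants per group", that is, 60 in total.

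Three other sections bear on it:
- Section 2.5 sets 1:1 randomisation.
- Section 2.7.1 defines BPI interference as an average on a 0 to 10 scale.
- Section 2.9 names the Student t-test (Mann-Whitney U if the data are not normal), calls a Cohen's effect size of 0.8 large, and plans a per-protocol analysis of those who completed treatment.

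Neither Section 2.8 nor any other section gives an SD or a standardised effect for BPI interference. Section 2.8 also does not say which test was used in the calculation, or whether it was one- or two-sided.

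**The concern.** There are two separate matters.

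The first is internal consistency. An evaluable total of 49 does not fit two equal groups, and the enrolment figure does not deliver 49 evaluable patients at the dropout rate the section itself assumes. Because Section 2.9 analyses completers, each dropout comes straight off the analysed number.

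The second is that the step from a 1.00-point difference to 49 patients needs an SD. The article presents a finished calculation, but a reader cannot check it. The stated 80% power depends on that missing value, and so does the reading of a non-significant result.

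**Working it through.** **Inputs.** Difference 1.00, α 0.05, power 80%, evaluable total 49, dropout 20%, final 30 per group (all Section 2.8); 1:1 allocation (Section 2.5); two-sample t-test (Section 2.9). Assumptions: two-sided testing as the main reading, with one-sided shown as the alternative, and a range of SDs.

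**Step 1: equal split.** 49 / 2 = 24.5. The nearest splits are 24/24 (48), 24/25 (49) and 25/25 (50). Only 48 and 50 are equal.

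**Step 2: dropout.**
- To keep 49 after 20% loss: 49 / (1 − 0.20) = 61.25, so 62 enrolled (31 per arm).
- What 60 enrolled leaves: 60 × 0.80 = 48 (24 per arm), one below 49.
- Where 60 may come from: 49 × 1.20 = 58.8, rounded up to 60 for equal groups. It also equals 48 / 0.80 = 60 exactly.
- Dropout that 60 can bear and still keep 49: (60 − 49) / 60 = 18.3%.

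**Step 3: can 49 be reproduced?** Not from the stated inputs. Solving backwards with the noncentral t distribution, where d = 1.00 / SD and the noncentrality is d × √(n₁n₂ / (n₁ + n₂)), gives the SD at which power is exactly 80%:

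| Split | Sides | d | Implied SD |
|---|---|---|---|
| 24/24 | two | 0.826 | 1.21 |
| 24/25 | two | 0.817 | 1.22 |
| 25/25 | two | 0.809 | 1.24 |
| 24/25 | one | 0.721 | 1.39 |

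On the two-sided reading, the minimum important difference is thus being treated as a standardised effect of about 0.82, just above the 0.8 that Section 2.9 calls large.

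**Step 4: cost of the dropout slip alone.** At SD 1.22, two-sided, power is 80.2% with 24/25 and 79.4% with 24/24, a loss of under one percentage point.

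**Step 5: dependence on the SD.** The SDs below are assumptions, not values from the article. Figures are for 24 per arm, two-sided; the detectable difference at 80% power is 0.826 × SD.

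| Assumed SD | Power for 1.00 | Detectable difference |
|---|---|---|
| 1.22 | 79% | 1.01 |
| 1.5 | 62% | 1.24 |
| 2.0 | 40% | 1.65 |

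**The case against.** The strongest reply is that the missing SD is an omission, not an error. It may stand in a fuller protocol or in the source cited for the 1.00-point difference, so the stated power may be right. That stands: the article neither confirms nor refutes 80%. The reply can go further. Section 3 plans to report changes, so the SD used may be that of change, which can be well below the raw SD when the two assessments are strongly correlated. Nothing in the article favours an SD of 1.5 or 2.0 over 1.22. This also stands, and it is why the table in the working is a range and not an estimate.

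A reader might infer from the odd total that the wrong test was run, for example a paired one, or that 49 was a per-arm number taken as a total. The article does not support either. A per-arm 49 conflicts with 30 per group. An odd total can also come from a legitimate between-group calculation: an ANCOVA with one covariate, α 0.05, 80% power and f = 0.41 (d = 0.82) returns 49. Section 2.9 does not name ANCOVA, so that too is only a possibility, but it shows that the odd number does not identify a mistake in the test. It still cannot be equally distributed.

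Finally, the dropout gap is one evaluable patient. That is true, and it limits the weight of the point, but the stated figures still disagree.

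**Conclusion.** The point holds as a should-fix. Two statements in Section 2.8 are wrong on their own figures: 49 cannot be divided equally, and 60 less 20% is 48, not 49. This rests on arithmetic alone, and its effect is small: 60 against 62 enrolled, 48 against 49 evaluable, about 79% against 80% power.

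The 80% power claim also cannot be reproduced. It requires an SD of about 1.22 if a two-sided two-sample t-test was used, or about 1.39 if one-sided, and neither the SD nor the sidedness is given. A reader might conclude that the trial is underpowered. The article does not show that; it shows only that power for a 1.00-point difference would fall quickly if the relevant SD were larger.

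**What to change.** Keep 60 patients and rewrite Section 2.8:

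1. Replace 49 with an even evaluable total. 48 (24 per arm) is the one that agrees with both 60 enrolled and 20% dropout.
2. Make the dropout sentence consistent. Either state 48 evaluable at 20% dropout, with the power or detectable difference that 24 per arm gives for the two-group comparison; or, if 49 is kept as the minimum number to be analysed, drop the claim of equal groups for it and state that 60 enrolled tolerates about 18% dropout.
3. Report the SD used, whether it is raw or of change, and its source, together with the test and the sidedness.

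The cost is one rewritten paragraph and no extra patients. The stated power or detectable difference may become less favourable once the SD is shown.

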### 2.9. Statistical Analysis

Data will be analyzed using the Statistical Package of Social Science (SPSS) program for Windows (version 26 IBM, Armonk, NY, USA). Categorical data will be expressed as frequency (percentage). Continuous variables will be presented as mean and standard deviation (SD). The normality of the data will be first tested with the Shapiro-Wilk test. Characteristics of both groups will be compared using the Chi-square test for categorical variables. For continuous variables, the Student *t*-test will be used for those with a normal distribution and the Mann-Whitney U test for nonparametric variables. All effect sizes will be interpreted according to Cohen’s conventions: 0.3 = small, 0.5 = moderate, and 0.8 = large. A per-protocol analysis will be performed including participants who completed the treatment plan. Statistical significance will be set at *p* < 0.05.

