### 2.6. Intervention

The experimental group will be included in an 8-week PIM program. This program will include pain neuroscience education, functional exercise, consisting of low-intensity strengthening exercises, and relaxation techniques. The Template for Intervention Description and Replication (TIDieR) checklist [33] will be used. The control group will receive a leaflet. Patients in both groups will be allowed to take pharmacological treatment (paracetamol or non-steroidal anti-inflammatory drugs) if needed and under the prescription of a physician. Patients’ evaluations will be conducted at baseline (T1) and immediately post-intervention (T2).

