## 3. Results

The results will be published as a peer-reviewed article. The authors intend to generate 3 tables summarizing the main results of this article. The first will be the table of descriptive characteristics of the sample. The second table will present the data of the comparison between groups at baseline for the primary outcomes. The third table will present the post-intervention outcome data, showing the intragroup and between-group changes, and expressing the effect size using Cohen’s d. In addition, a figure with the flow diagram will be added.

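### Section 2.9 names only unadjusted between-group tests, picked by a normality pre-test, and does not use the baseline score as a covariate; one prespecified ANCOVA per outcome would be more precise and keep the effect a mean difference

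*Protocol article*

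**What the plan says.** Section 2.9 opens the inferential part with a gate: "The normality of the data will be first tested with the Shapiro-Wilk test". It continues: "Characteristics of both groups will be compared using the Chi-square test for categorical variables". For continuous variables, Student's t "will be used for those with a normal distribution and the Mann-Whitney U test for nonparametric variables". No regression model, baseline adjustment or covariate adjustment is named. The section gives neither the threshold for the normality test nor whether it is applied to each arm, to the pooled variable or to residuals.

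Three other places bear on this:

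- Section 2.6 schedules assessments at baseline (T1) and directly after the intervention (T2), so each outcome has a baseline score.
- Section 2.8 bases the sample size on a difference of 1.00 in BPI interference.
- Section 3 says that the third table will give the post-intervention data, "showing the intragroup and between-group changes, and expressing the effect size using Cohen’s d".

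**The concern.** Read literally, the test sentences concern the characteristics of the two groups, not the treatment effect. But they are the only between-group tests in the article, so the natural reading is that they also serve the outcomes. Two weaknesses follow.

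**Precision.** The T1 score of the same scale is usually the strongest predictor of the T2 score, and it is collected anyway. An unadjusted test of T2 ignores it. An unadjusted test of change subtracts it with a coefficient fixed at 1, which over-corrects whenever the true slope is smaller. ANCOVA estimates the slope.

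**What is being tested.** The 1.00-point MCID and Cohen's d are both mean-difference quantities. Mann-Whitney compares ranks. If the gate selects it for an outcome, the p-value and the reported effect size for that outcome answer different questions. Which question is answered can differ between outcomes and is settled by the trial's own data.

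With about 24 to 30 patients per arm there is little precision to spare.

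**Working it through.** **Inputs from the protocol.** Difference 1.00 on BPI interference, alpha 0.05, power 80%, 49 in total before dropout, 20% dropout, 30 per arm (Section 2.8). Alpha is taken as two-sided; the article does not say.

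**Assumptions not in the protocol.** The SD, the T1–T2 correlation r (0.3, 0.5, 0.7), and equal SDs at T1 and T2. Analysed per arm: 30 × 0.8 = 24.

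**Step 1: the plan's own figure.** No SD is given, so 49 cannot be reproduced forwards. Solving the two-sample noncentral-t power equation with 24 and 25 patients for 80% power gives d = 0.817, so SD = 1.00/0.817 = 1.22. With 24 per arm and SD 1.22 (d = 1/1.22 = 0.820), power for T2 alone is 79%.

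**Step 2: variance of each estimator relative to T2 alone.**

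- Change score: 2(1 − r)
- ANCOVA: 1 − r²
- Difference between them: 2(1 − r) − (1 − r²) = (1 − r)², which is never negative. So the change score is never asymptotically more precise than ANCOVA.
- The change score is worse than T2 alone when 2(1 − r) > 1, that is, when r < 0.5.

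| r | Change score | ANCOVA |
|---|---|---|
| 0.3 | 1.40 | 0.91 |
| 0.5 | 1.00 | 0.75 |
| 0.7 | 0.60 | 0.51 |

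**Step 3: power for 1.0 point, 24 per arm, two-sided.** The effective standardised difference is (1/SD)/√(variance ratio), with 46 degrees of freedom (45 for ANCOVA). At SD 1.22 and r = 0.3, for example, it is 0.820/√1.40 = 0.693 for change and 0.820/√0.91 = 0.859 for ANCOVA.

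| SD | r | T2 alone | Change score | ANCOVA |
|---|---|---|---|---|
| 1.22 | 0.3 | 79% | 65% | 83% |
| 1.22 | 0.5 | 79% | 79% | 89% |
| 1.22 | 0.7 | 79% | 95% | 97% |
| 2.0 | 0.3 | 40% | 30% | 43% |
| 2.0 | 0.5 | 40% | 40% | 50% |
| 2.0 | 0.7 | 40% | 59% | 66% |

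The SD of 2.0 is purely illustrative, to show the range. The ANCOVA figures ignore the small loss from chance baseline imbalance.

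**Step 4: the gate.** Simulation with 24 per arm and 5,000 runs per scenario, applying Shapiro-Wilk in each arm at 0.05 and then t or Mann-Whitney:

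| Data | Mann-Whitney chosen | Type I error, gated | t fixed | Mann-Whitney fixed |
|---|---|---|---|---|
| Normal | 10% | 5.5% | 5.4% | 5.4% |
| Beta(2,4), mild skew | 27% | 5.6% | 5.3% | 5.2% |
| Lognormal, sigma 0.5 | 85% | 5.5% | 5.0% | 5.0% |

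Simulation error is √(0.05 × 0.95/5000), or about 0.3 percentage points. The gate therefore has little effect on the error rate. What it changes, in anything from a tenth to most of the trials simulated, is the quantity tested.

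**The case against.** The strongest reply has five parts.

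**Baseline is not thrown away.** A reader might infer from Section 2.9 alone that the T1 scores are discarded, and so quote a gain from 79% to 97%. Section 3 does not support that: between-group changes use T1. Against change scores the gain at r = 0.7 is from 95% to 97% at SD 1.22, and from 59% to 66% at SD 2.0. This stands. The claim is only that T1 is not a covariate, and the gain over change scores is large only at low to moderate r.

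**The rule is stated in advance and error control is sound.** It would be tempting to say that the gate inflates false positives; the simulation does not show that. Nor can one say firmly how often a test will switch, because that depends on whether normality is checked by arm or pooled, which the article leaves open. With clearly skewed data the gate can even help: in the lognormal simulation, power against a 0.818 SD shift was 91% gated and 80% with t alone. This stands as a defence of validity and power. It does not cure the mismatch between a rank test and an effect stated as a mean difference.

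**The sentence may cover only baseline characteristics.** It may. In that case the article names no test for the treatment effect, and a statistical analysis plan not shown could supply one. The uncertainty is real, but the wording still needs to change.

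**The covariables in Section 2.7.2 have no stated role.** A reader might count that as a further fault. How they are used is commonly left to an analysis plan, so it is not part of this point.

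**Within-group changes.** A reader might expect within-group p-values and object to regression to the mean. No paired test is stated, and regression to the mean affects both randomised arms alike.

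**Conclusion.** The point holds as one of precision and clarity, not as a threat to validity. The only between-group tests named for continuous variables are unadjusted and chosen variable by variable by a normality pre-test. Applying them to the treatment effect is an inference, though the article offers nothing else. T1 enters at most as a subtraction. Compared with change scores, ANCOVA gains about 18, 10 and 2 percentage points of power at r = 0.3, 0.5 and 0.7 (SD 1.22). Compared with T2 alone it gains about 4, 10 and 18. ANCOVA is the best of the three throughout this range, and which alternative is worse depends on an r that the article does not give. These sizes rest on an SD back-solved from 49, equal SDs at both visits and 24 analysed per arm.

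**What to change.** In Section 2.9, replace the gated choice of test, for the outcomes, with one model per outcome: ANCOVA of the T2 score on arm and the T1 score of the same scale. Report the adjusted between-group mean difference with its 95% confidence interval. Remove the Shapiro-Wilk gate. Keep a rank-based or bootstrap analysis as a sensitivity analysis only. Name any further covariate in advance; do not leave it optional, since an open covariate list would again let the data shape the model. State separately that descriptive comparisons of group characteristics are not the treatment-effect analysis.

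The cost is one degree of freedom per outcome model and a change of analysis wording. No extra data are needed, and the model runs in the SPSS version already named.

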The functional exercise program will consist of 3 different parts. The first part will be a warm-up focused on joint mobilization. The second part will focus on functional exercises consisting of low-intensity strengthening exercises of the main muscle groups. This section will have four main objectives: core stability, postural positioning, limb muscle strength, and functional activities. The proposed exercises have been previously used in this population demonstrating their reliability and safety [34,35]. Some of them are the bodyweight squat, hip thrust, rowing, front plank, lateral squat, and chest press. However, the exercises, the number of sets and repetitions, and rest periods will be individually adapted to each patient depending on their needs, severity of pain, and physical ability with different levels of progression. The exercises will be adapted so that they can be performed at home without the need for specific materials. Only when the patient can perform the exercises with the correct technique and without effort, the exercises will be progressed to more demanding exercises or a higher training load.

Finally, relaxation techniques will be performed. Relaxation strategies will include practicing mindfulness and breathing control, cultivating body awareness and muscle tension management, as well as awareness of thoughts and emotions related to pain.

The mindfulness practice will focus on trying to make the patient aware of the present moment. To do this, the patient will be asked to focus their attention on the bodily sensations they have at that moment and on their breathing rhythm. The goal is to allow the patient to disconnect from the persistent pain, focusing on healthy sensory experiences. Breathing control is a fundamental technique to improve the stress response. Participants should practice deep and conscious breathing, which will allow a more efficient oxygen intake and carbon dioxide output, thus contributing to reducing the activation of the sympathetic nervous system and therefore the perception of pain.

The body awareness and muscle tension management techniques will be performed through exercises that allow patients to develop a greater awareness of areas of tension. Increased body awareness will allow patients to become proactively involved in pain management.

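### Section 2.9 names Student's t-test as the only parametric comparison, while the completer-only set is likely to leave unequal arms; naming Welch's t-test is a minor, cheap improvement

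*Protocol article*

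**What the plan says.** Section 2.9 checks normality with Shapiro-Wilk and then assigns tests. Categorical variables get the chi-square test. For continuous variables, the Student t-test "will be used for those with a normal distribution and the Mann-Whitney U test for nonparametric variables". The passage opens with "Characteristics of both groups will be compared using the Chi-square test for categorical variables", so read literally it concerns group characteristics. However, section 3 promises a post-intervention table "showing the intragroup and between-group changes, and expressing the effect size using Cohen’s d", and no other between-group test is named anywhere. It is reasonable to take the same tests as the treatment comparison.

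On the analysis set, section 2.9 states: "A per-protocol analysis will be performed including participants who completed the treatment plan". Section 2.6.1 gives the PIM arm eight weeks of two face-to-face and two home sessions per week. Section 2.6.2 gives controls standard medical care and a leaflet, without monitoring by a therapist. Section 2.8 plans 30 per group with 20% dropout, not split by arm. No SD is given for any outcome.

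**The concern.** The pooled t-test tolerates unequal variances well when the arms are about the same size, and poorly when they are not. If the smaller arm has the larger variance, the pooled standard error is too small; if it has the smaller variance, the standard error is too large.

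The 1:1 allocation would normally give protection, but the completer-only set is likely to remove some of it. The PIM plan has 8 × (2 + 2) = 32 sessions to complete, while controls have almost nothing to fail. The only preliminary check named, Shapiro-Wilk, does not look at variances. At stake is the calibration of p-values, and of any confidence intervals, for the Brief Pain Inventory, Pain Catastrophizing Scale, Tampa scale and WHODAS comparisons, all of which are listed as primary outcomes.

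**Working it through.** **The plan's own figures.** The article states no error rate for unequal variances, so there is none to reproduce. Section 2.8 rests on the "minimum clinically important difference (MCID) of the BPI interference estimated to be 1.00" with 80% power and α = 0.05, giving 49 in total, but without an SD. Solving backwards for a two-sided t-test with 24.5 per arm gives d = 0.817, so SD = 1.00 / 0.817 = 1.22. That SD is an inference and is used below only for power.

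**Scenarios for arm sizes.** Section 2.8 gives 60 randomised, and 20% of 60 is 12 lost, leaving 48.
- Loss shared equally: 24 v 24.
- PIM loses 20% (6 of 30), controls none: 24 v 30.
- All 12 losses in PIM: 18 v 30, the extreme case.
- An intermediate case: 20 v 30.

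The PIM:control SD ratio r is an assumption, shown from 0.67 to 2.

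**Why size and variance interact.** With the control SD set to 1:
- true variance of the difference = r²/n₁ + 1/n₂
- variance that the pooled test expects = [(n₁ − 1)r² + (n₂ − 1)] / (n₁ + n₂ − 2) × (1/n₁ + 1/n₂)

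Examples:
- 24 v 24, r = 2: true 5/24 = 0.208; pooled 2.5 × 2/24 = 0.208. No error in the SE.
- 24 v 30, r = 1.5: true 0.0938 + 0.0333 = 0.1271; pooled (51.75 + 29)/52 × 0.075 = 0.1165. SE ratio √(0.1165/0.1271) = 0.957, so about 4% too small.
- 18 v 30, r = 2: true 0.2222 + 0.0333 = 0.2556; pooled (68 + 29)/46 × 0.0889 = 0.1874. SE ratio 0.856, so about 14% too small.
- 18 v 30, r = 0.67: true 0.0583; pooled 0.0708. SE ratio 1.10, so about 10% too large.

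**False-positive rate of the pooled test** (simulated normal data, equal means, two-sided 5%, 400,000 runs per cell; repeat runs differ by about 0.1 point):

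| PIM v control | r = 0.67 | r = 1 | r = 1.25 | r = 1.5 | r = 2 |
|---|---|---|---|---|---|
| 24 v 24 | 5.1% | 4.9% | 5.0% | 5.1% | 5.2% |
| 24 v 30 | 4.1% | 5.0% | 5.6% | 6.1% | 6.8% |
| 20 v 30 | 3.5% | 5.0% | 6.1% | 7.1% | 8.4% |
| 18 v 30 | 3.2% | 5.0% | 6.4% | 7.5% | 9.4% |

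Welch's test gives 4.9–5.1% in every cell. A shift in the mean does not alter these rates as interval non-coverage, so pooled 95% intervals at 18 v 30 would cover about 93.6% down to 90.6% for r from 1.25 to 2.

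**Choosing by Levene's test.** Letting Levene's test select the t-test version gave 5.4% and 5.5% at 24 v 30 (r = 1.25 and 1.5) and 6.0% at 20 v 30 (r = 1.5). In those cells Levene's test detected the difference in only 18%, 46% and 44% of runs. Pre-testing is therefore not a full remedy.

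**Power cost of Welch with equal variances** (difference 1.00, SD 1.22): 78.4% to 78.0% at 20 v 28, and 76.8% to 76.2% at 18 v 30. A longer run of the first gave 78.2% to 77.9%.

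**The case against.** The strongest objection is that the article does not use the words pooled or equal variances. SPSS prints both versions, and which one is reported could be left to an analysis plan that is not shown. This stands in part: pooling is inferred from the test's usual meaning. But the article does more than stay silent. It names a specific test, and that name ordinarily denotes the pooled version.

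A reader might go further and infer that the plan raises the false-positive rate to 6–9%. The documents do not support that.
- Neither condition is quantified. There are no SDs and no dropout by arm, completion of the treatment plan is not defined in section 2.9, and controls can also be lost before T2.
- A larger PIM variance is conjecture. Section 2.6.1 says that "rest periods will be individually adapted to each patient depending on their needs, severity of pain, and physical ability"; this describes the exercise prescription and says nothing about the spread of outcomes. Tailoring could narrow the spread, and the pooled test would then be conservative.
- Controls are not simply untreated. They receive standard care and a leaflet, and section 2.6 allows both arms prescribed analgesics.
- The upper end needs all 12 expected losses in PIM, none among controls, and twice the SD.
- If PIM changes nobody's outcome and completion is not selective, the SDs are equal and the pooled test holds 5% at any split.

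Nor does the error specifically favour PIM: in a two-sided test it is spread over both directions.

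That last condition matters for error under a strict null. It matters less for intervals: if PIM works unevenly, their coverage is affected whatever the mean effect. Finally, selective completion is mainly a problem of bias, which no choice of t-test removes.

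**Conclusion.** The point holds as a minor improvement. Section 2.9 names a test whose robustness depends on similar arm sizes, and the same section defines an analysis set likely to make them unequal. The departure from 5% is nil to negligible with equal arms or equal SDs. It is about 5.6–6.8% at 24 v 30 and about 6.3–9.5% at 18 v 30 if the PIM SD is 1.25–2 times larger, and about 3–4% at these splits if the SD ratio is 0.67. These figures assume normal data, a two-sided test (sidedness is not stated), and SD ratios and completer splits that the article does not give. They describe what could happen and do not predict this trial's error rate. Welch's test keeps about 5% in all the cases examined. The larger threat in the same sentence of the plan is selection by completion, which is a separate matter.

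**What to change.** In section 2.9, replace the Student t-test with Welch's (unequal-variance) t-test, without a preliminary Levene test, wherever the plan uses the t-test. In SPSS this is the row for equal variances not assumed, which is already printed.

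Leave the Mann-Whitney branch to be considered separately; this change does not extend Welch's test to variables that the plan sends there. No provision for robust regression errors is needed, because no regression is planned.

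The cost is one phrase in the text and under one percentage point of power if the variances are in fact equal. The change does not repair the selection bias of the completer-only set.
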